### Randomization

The unit of randomization was the patient. We chose to randomize individual patients rather than physicians because the intervention was intended to operate at the patient level (affecting patient knowledge, attitudes, self-efficacy, and behaviors) and because the improved precision of estimated intervention effects that arises from randomizing patients from the same physician to different study arms was felt to outweigh the increased risk of bias from between-arm contamination that arises from communication among patients.

During the previsit computer session, patients were randomized to an intervention after answering questions about their gender and race/ethnicity, via a computerized randomization algorithm incorporated into the multi-media computer interface. To ensure balanced assignment by gender and race/ethnicity, the computer randomization program stratified subjects into one of eight groups: black female, black male, Hispanic female, Hispanic male, white female, white male, other female, other male. Computerized racial/ethnic group assignment was based on the following decision rule: 1) Hispanic trumps all other selections, 2) for non-Hispanics, African-American trumps all (e.g., someone selecting African-American and Asian for race would be put into the African-American randomization category); and 3) for people not selecting black, “other” categories trump white (e.g., if someone selects Native American and white, they are randomized as other). Within each of these eight categories, patients were randomly allocated in equal proportions to one of the three study arms, in randomly permuted blocks of nine subjects.

### Procedures on Day of office visit: post-randomization

Immediately after being randomized and prior to revealing the assigned intervention to the patient during the previsit computer session, the patient was queried a second time regarding current use of antidepressant medications, an exclusion criterion for participation in the study that was first assessed and used as an exclusionary criteria during the initial telephone screening. Patients reporting current use to this inquiry were informed that they did not meet eligibility rules for continuing in the study and were thanked for their participation. Assessing this exclusion criterion *after* randomization occurred was a design flaw that resulted in a small fraction of randomized patients being excluded from further study. Notwithstanding this flaw, the exclusions that resulted could not, as a practical matter, have been affected by the randomized assignment and hence we do not expect that this flaw can bias the estimates of between-arm contrasts.

After intervention assignment, patients continued to answer baseline (previsit, preintervention) survey questions for use in targeting/tailoring and to assess baseline health status. Regardless of assignment, all patients answered the same series of questions, including items on income, visit agenda (intention to request treatment vs. intention only to discuss depression vs. no intention to discuss depression); treatment preferences; depression causal attributions; communication self-efficacy and stigma used for tailoring or targeting interventions. The computer software was designed to automatically store responses in a computer database and to use these responses to customize (i.e. target/tailor) assigned interventions accordingly. After completing the pre-visit questionnaire, the patient watched his or her randomly assigned and appropriately customized intervention: a targeted PSA, the tailored IMCP, or the (uncustomized) control video. The PSA and control video were approximately 2.5 minutes in length. Typically, patients assigned to the IMCP spent between 2 (10^th^ percentile) and 15 (90^th^ percentile) minutes viewing educational materials.

After patients viewed the material and exited the computer session, they waited to be called in for their scheduled office visit. Patients who reported recent (<2 weeks) suicidal thoughts were flagged by the computer so that the RA could involve the patient in the decision to notify the physician with a written message about their risk for suicide. The RA did this by delivering a letter to the physician prior to the visit alerting the physician to the patient’s status. Beyond these efforts, study personnel did not attempt to control patient-PCP communication content or force discussion of depression treatment.

### Procedures for post-visit assessments

Immediately following the office visit, subjects returned to the tablet PC to complete a post-visit questionnaire, which contained many of the same items as on the pre-visit questionnaire plus questions about the encounter (e.g., whether they asked about depression and/or depression-related care and whether the physician prescribed an antidepressant, made a mental health referral, or arranged for follow-up). Twelve weeks after the index visit, RAs telephoned patients reporting PHQ-8 scores of ≥ 5 *either* during screening *or* on the day of the index visit to assess treatment adherence, severity of depressive symptoms, and health status using a scripted follow-up interview.

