### Sub-study 2: patients *without* clinically significant depressive symptoms

This sub-study involves a sample of approximately 300 patients whose baseline PHQ-9 scores were less than 5. The aims of this sub-study are:

(1) To examine whether the interventions are associated with (a) detrimental *process of care* effects (including unnecessary initial antidepressant prescriptions, physician rating of greater effort during visit, longer visit duration), and/or (b) decrements in patient functioning (specifically, worse physical health at 12 week follow-up). It is hypothesized that the active interventions will not result in detrimental outcomes in those without evidence of significant depression.

(2) To examine whether the interventions may lessen perceived depression stigma among non-depressed persons. It is hypothesized that the active interventions will result in reduced stigma after the index visit among patients without evidence of significant depression.

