**Sub-study 2: patients*****without*****clinically significant depressive symptoms (baseline PHQ-9 < 5)**			
Process of care			
Antidepressant prescription (over-treatment)	X		PQ, PCPQ, MRR
Distraction effects			
Index office visit length	X		
Patient request for depression treatment	X		
Physician visit effort	X		
Patient function			
SF-12 Physical Component Summary score (potential toxicity, i.e. reduced function)		X	PQ
Patient perceived depression stigma (potential reduction)	X	X	PQ

* Sub-study 1 primarily powered to examine this outcome; research evidence indicates PHQ-9 scores ≥ 10 are associated with significant life impairment (e.g. reduced functional abilities) and a strong likelihood of clinical depression, while scores of 5–9 are more equivocal in this regard.

^†^ Not an evidence-based element of care, but endorsed in prevailing clinical practice guidelines.

^‡^ Includes all PHQ-9 items except the item concerning self-harm thoughts.

Abbreviations:

*AMEP2*, Activating Messages for Enhancing Primary Care Practice; *MRR*, medical record review; *NA*, not applicable (participants in this sub-study are not followed up); *PCP*, primary care provider; *PCPQ*, PCP questionnaire; *PHQ*, Patient Health Questionnaire; *PQ*, patient questionnaire.

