This project’s emphasis on initial care of depression is based on evidence that depression in primary care often goes undiagnosed [13], that clinically mild depression not infrequently evolves to major depression within a year [21], and that even detected depression is often under-treated in primary care [22,23]. Although subsequent care (including attention to patient adherence, careful monitoring of depression treatment response, and avoidance of clinical inertia) is critically important, none of this is possible in the absence of accurate diagnosis and appropriate initial care.

In conducting the trial, we encountered several noteworthy challenges and limitations:

•To accrue the 867 patients ultimately enrolled in the study, we attempted to reach more than 15,000 patients by telephone and screened over 6000. In settings where local ethics boards required an opt-out process prior to any telephone contact (allowing patients to return a postcard indicating their desire not to be screened), screening was even less efficient. Yet we were ultimately successful in enrolling a sample that appears representative of the underlying population of interest, at least in the clinics studied.

•Our protocol required a substantial time investment by patients, as they were required to arrive in clinic one hour prior to their scheduled appointment. In a small proportion of encounters, patients arrived too late to administer the intervention and accompanying surveys, and they had to be rescheduled. Most of the pre-visit time required of patients was for informed consent and survey administration; the PSA and control videotapes were less than three minutes in length, and the median time patients spent with the IMCP was 5 minutes.

•Enrollment was limited to English-speaking patients, and English-speaking Latinos constituted less than 10% of the sample. Generalizability of the findings to this important demographic group will be restricted.

In summary, the results of this RCT will address the question of whether multimedia patient engagement programs for depression improve processes and outcomes of care for depressed persons. In addition, the trial will compare the relative effectiveness of targeted versus tailored interventions. Finally, the study will address whether the interventions are “safe” (i.e. that they do not worsen processes or outcomes of care) and could even have benefits (e.g. fostering less stigmatized views of depression) among non-depressed persons.

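### The 12-week call rule never reaches patients who stay below PHQ-8 5, yet Sub-study 2 sets 12-week harm and stigma outcomes for all its patients

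*Protocol article*

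**What the plan says.** - **Membership.** The Sub-study 2 section describes about 300 patients "whose baseline PHQ-9 scores were less than 5". A Table 1 footnote defines the PHQ-8 as the PHQ-9 without the self-harm item.
- **Harm aim.** Aim 1(b) of that section is to look for "decrements in patient functioning (specifically, worse physical health at 12 week follow-up". Table 1 carries this as "SF-12 Physical Component Summary score (potential toxicity, i.e. reduced function"), marked at 12 weeks. Table 1 also marks stigma at 12 weeks for this sub-study. Aim 2 states its stigma hypothesis only for the time after the index visit.
- **Call rule.** Under Procedures for post-visit assessments: "Twelve weeks after the index visit, RAs telephoned patients reporting PHQ-8 scores of ≥ 5". For this rule the qualifying score is one given "during screening *or* on the day of the index visit".
- **Legend.** The Table 1 abbreviations explain NA as "not applicable (participants in this sub-study are not followed up"), without naming the sub-study. NA appears nowhere in the table as reproduced.
- **Power.** The sample-size section gives more than 80% power for pairwise differences of 0.4 sd in means with 102 per arm in the non-depressed sub-study, with no exception for 12-week outcomes.
- **Intended conclusion.** The Discussion says the study will address whether the interventions are safe in non-depressed persons, in the sense "that they do not worsen processes or outcomes of care".

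**The concern.** The rule that puts a patient in Sub-study 2 and the rule that triggers a 12-week call work against each other. A low score on the visit day gives membership, and a score of 5 or more gives the call. A Sub-study 2 patient therefore enters 12-week follow-up mainly through an earlier, higher screening score. The clearest non-depressed patients, those below 5 on every occasion, have no 12-week data under the rule as written.

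The SF-12 physical score is the only patient-function harm measure in this sub-study, and the stated hypothesis is that no harm will be found. In a small, selected subset a non-significant difference is the likely result even if a moderate harm exists. It could then be read as reassurance about all non-depressed patients.

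**Working it through.** **Step 1. Who can be called.**
- PHQ-8 is PHQ-9 less one non-negative item, so PHQ-8 ≤ PHQ-9. Baseline PHQ-9 < 5 implies previsit PHQ-8 < 5.
- The previsit score can therefore never trigger a call for a Sub-study 2 patient.
- Two routes remain: screening PHQ-8 ≥ 5 one to two weeks earlier, or a post-visit PHQ-8 ≥ 5 on the same day. The second is uncertain, because Table 1 marks a post-visit PHQ-8 only under Sub-study 1. If it counts, entry to follow-up depends on a score taken after the intervention.

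**Step 2. Reproduce the stated power.** For a two-sided 5% test (stated for Sub-study 1, assumed here), power ≈ Φ(δ√(n/2) − 1.960).
- With n = 102 and δ = 0.4: 0.4 × √51 = 2.857, 2.857 − 1.960 = 0.897, and Φ(0.897) = 0.815. The t-test gives 0.811. The stated figure reproduces.
- The number needed for 80% is 2 × ((1.960 + 0.842)/0.4)² = 98.1, so 99 per arm. There is almost no room for missing follow-up.

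**Step 3. The callable share f.** The documents do not give it. It was modelled by simulating correlated screening and index-visit PHQ-8 scores and computing P(screening ≥ 5 given index < 5). The inputs come from Table 2: screening means 7.9, 7.0, 7.2 (sd 5.4, 5.1, 5.4), index means 7.9, 6.7, 7.1 (sd 5.5, 5.3, 5.4), correlations 0.84, 0.84, 0.86. Arms were weighted by their Sub-study 2 sizes (90, 109, 109).
- Normal margins: 27%.
- Beta-binomial margins on 0 to 24: 24%.
- Gamma margins, pooled mean 7.25, sd 5.4, correlation 0.82 to 0.88: 19% to 24%.
- The lowest value across the modelling variants was about 18%.

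The range used is 18% to 27%: 0.18 × 308 ≈ 55 to 0.27 × 308 ≈ 83 patients.

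**Step 4. Power for 12-week means.** Per-arm n = 102f. The difference detectable with 80% power is (1.960 + 0.842) × √(2/n).

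| Share f | n per arm | of 308 | Power at 0.4 sd, normal | Power, t-test | Detectable difference (sd) |
|---|---|---|---|---|---|
| 10% | 10.2 | 31 | 0.145 | 0.137 | 1.24 |
| 18% | 18.4 | 55 | 0.227 | 0.219 | 0.92 |
| 20% | 20.4 | 62 | 0.247 | 0.238 | 0.88 |
| 27% | 27.5 | 83 | 0.317 | 0.308 | 0.76 |
| 30% | 30.6 | 92 | 0.346 | 0.337 | 0.72 |
| 50% | 51.0 | 154 | 0.524 | 0.516 | 0.55 |
| 100% | 102 | 308 | 0.815 | 0.811 | 0.39 |

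No loss to follow-up is included, so these figures are upper limits for each share.

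**The case against.** **The documents do not show which text is wrong.** The call rule may be incompletely described, or the aim and Table 1 may be. The overview of the design says without condition that patients completed 12-week surveys. This stands, and it is why the fix has two branches. A reader might infer that aim 1(b) and its table rows should simply be deleted. The documents do not support that, and removing a stated harm aim after accrual would look like selective outcome removal.

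**The subset is not worthless.** A reader might infer that the 12-week harm outcome cannot be estimated at all. That is too strong. Some 55 to 83 people is a usable, if small, group. If entry is by screening PHQ-8, selection precedes randomisation, so the contrast between arms within the subset keeps its internal validity. What is lost is precision and relevance to patients who were never above the cut-off. Nor need the called patients have truly improved: with a correlation near 0.85, crossing a cut-off of 5 can be measurement variation.

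**The power statement is not false as written.** It names no 12-week outcome and holds for index-visit and post-visit means. This stands. It only fails to carry over to 12 weeks.

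**The legend is weak evidence.** A reader might take it as proof that Sub-study 2 had no follow-up. It does not name the sub-study and may be a leftover. The contradiction does not need it.

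**The call content should not be pressed.** The interview is summarised as being "to assess treatment adherence, severity of depressive symptoms, and health status using a scripted follow-up interview". A reader might infer that stigma was not asked at 12 weeks. A one-line summary of a script that is not shown cannot establish that, and the Sub-study 1 outcomes list stigma at 12 weeks expressly.

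**Conclusion.** The contradiction is real and follows from the article's own definitions. As written, Sub-study 2 patients below 5 at every measurement are never called, while aim 1(b) and Table 1 set 12-week outcomes for the whole sub-study.

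The size rests on an assumed callable share. The modelled 18% to 27% uses moments pooled over all enrolled patients, who were sampled at screening with score-dependent probabilities, so the point figures are approximate. The direction is not in doubt: power at 0.4 sd is about 14% at a share of 10%, 22% to 32% over the modelled range, and 52% at a share of 50%.

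The reach is limited. The antidepressant noninferiority test, the visit-process measures and post-visit stigma are unaffected. The 12-week stigma outcome rests on Table 1 alone. The Discussion poses safety as a question to be answered, not as a result. The design as described can answer the process part for non-depressed patients, but it cannot answer the 12-week part for the sub-study as a whole.

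**What to change.** Reconcile the Sub-study 2 aims, Table 1 and the section on post-visit assessments, after checking who was in fact called.

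**If the call rule is accurate:**
- Keep aim 1(b) visible. State that the Sub-study 2 12-week outcomes are exploratory and come from a selected subset, defined by the pre-randomisation screening PHQ-8 of 5 or more.
- Report the actual n per arm, with confidence intervals rather than a bare significance test.
- State that the 102-per-arm, 0.4 sd power applies only to index-visit and post-visit means.
- Limit the safety conclusion in the Discussion for non-depressed patients to index-visit processes and post-visit stigma.
- Say whether a post-visit PHQ-8 could trigger a call. If so, keep patients who entered only by that route out of the subset.

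**If all Sub-study 2 patients were called:** correct the call rule and the Table 1 legend. The outcomes can then stand.

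The cost is wording, a count from the follow-up log and, in the first case, a narrower safety conclusion. No new data are needed.

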**Methods/design:**

The Activating Messages to Enhance Primary Care Practice (AMEP2) Study is a stratified randomized controlled trial comparing two computerized multimedia patient interventions --- one targeted (to patient gender and income level) and one tailored (to level of depressive symptoms, visit agenda, treatment preferences, depression causal attributions, communication self-efficacy and stigma)--- and an attention control. AMEP2 consists of two linked sub-studies, one focusing on patients with significant depressive symptoms (Patient Health Questionnaire-9 [PHQ-9] scores ≥ 5), the other on patients with few or no depressive symptoms (PHQ-9 < 5). The first sub-study examined effectiveness of the interventions; key outcomes included delivery of components of initial depression care (antidepressant prescription or mental health referral). The second sub-study tracked potential hazards (clinical distraction and overtreatment). A telephone interview screening procedure assessed patients for eligibility and oversampled patients with significant depressive symptoms. Sampled, consenting patients used computers to answer survey questions, be randomized, and view assigned interventions just before scheduled primary care office visits. Patient surveys were also collected immediately post-visit and 12 weeks later. Physicians completed brief reporting forms after each patient’s index visit. Additional data were obtained from medical record abstraction and visit audio recordings. Of 6,191 patients assessed, 867 were randomized and included in analysis, with 559 in the first sub-study and 308 in the second.

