### Power calculations and sample size

By setting target sample sizes of 170 subjects per arm, the effectiveness sub-study was designed to provide 80% power to detect between-arm (pairwise) differences in the proportion receiving CIDC of 15 percentage points and standardized differences of 0.3 standard deviations (sd) in the mean levels of continuous outcomes, under two-sided testing with alpha = 5% [71]. For the sub-study focusing on non-depressed patients, the target enrollment of 102 subjects per arm provides 80% power to reject the noninferiority null hypothesis that exposure to an experimental intervention groups (N = 204 in the PSA/IMCP groups) is associated with at least a 3.5 percentage point increase in the extremely low risk anticipated for antidepressant prescribing in the control group (N = 102), under one-sided testing with alpha = 5% and assuming that the true risk is 1% in each of the three groups [72]. For pairwise comparisons of means, a sample size of 102 in each arm of the non-depressed sub-study provides greater than 80% power to detect differences of 0.4 sd [71].

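### The 12-week call rule reaches only part of Sub-study 2, although aim 1(b) and Table 1 set 12-week outcomes for all of it

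*Protocol article*

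**What the plan says.** Three places in the protocol article bear on who has 12-week data in the non-depressed sub-study.

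- **Who is called.** Under Procedures for post-visit assessments: "RAs telephoned patients reporting PHQ-8 scores of ≥ 5 *either* during screening *or* on the day of the index visit". No other section describes a 12-week contact for the remaining patients.
- **What is to be measured.** The Sub-study 2 section covers patients with a baseline PHQ-9 below 5. Aim 1(b) is to look for "decrements in patient functioning (specifically, worse physical health at 12 week follow-up", and the hypothesis is that "the active interventions will not result in detrimental outcomes in those without evidence of significant depression". Table 1 lists "SF-12 Physical Component Summary score (potential toxicity, i.e. reduced function" for Sub-study 2 in the 12-week column and marks perceived stigma both post-visit and at 12 weeks. Neither place limits these outcomes to a subset.
- **Power.** Under Power calculations and sample size: "a sample size of 102 in each arm of the non-depressed sub-study provides greater than 80% power to detect differences of 0.4 sd". No outcome or time point is named.

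The Table 1 footnote defines the PHQ-8 as the PHQ-9 without its self-harm item.

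**The concern.** The call rule and the Sub-study 2 outcomes do not fit together. Physical health at 12 weeks is that sub-study's only 12-week harm outcome. Followed as written, the plan yields it only for patients who had symptoms at the screening call and had dropped below the threshold by the visit. Patients below 5 on both occasions, who also belong to Sub-study 2, contribute nothing.

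The hypothesis is one of no detriment. A noninferiority margin is given only for antidepressant prescribing; every other outcome is assessed by Wald tests and 95% confidence intervals. The Discussion says the trial will address whether the interventions are safe, including for outcomes of care. A non-significant 12-week contrast in a small, selected group could then be taken as evidence of no harm in non-depressed patients generally, which it could not support.

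**Working it through.** **1. The logic of the rule.** PHQ-9 = PHQ-8 + self-harm item, and that item is never negative. Hence previsit PHQ-9 < 5 implies previsit PHQ-8 < 5. The previsit score therefore cannot trigger a call for anyone in Sub-study 2, which leaves a screening PHQ-8 of 5 or more.

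**2. The plan's own power figure.** Inputs: 102 per arm, d = 0.4 SD, two-sided 5% (stated for Sub-study 1, assumed to apply here).

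- Power = Φ(d·√(n/2) − 1.960) = Φ(0.4·√51 − 1.960) = 0.815 (0.811 by the t-test). The stated figure reproduces.
- Required n = 2(1.960 + 0.842)²/0.4² = 98.1, so 99 per arm. Nearly the whole sub-study is needed.

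**3. An illustrative share called.** The article gives no count. Inputs from Table 2, taking the enrollment PHQ-8 as the screening score:

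| Arm | PHQ-9 < 5 (n) | PHQ-8 enrollment, mean (SD) | PHQ-8 index visit, mean (SD) | r |
|---|---|---|---|---|
| IMCP | 90 | 7.9 (5.4) | 7.9 (5.5) | 0.84 |
| PSA | 109 | 7.0 (5.1) | 6.7 (5.3) | 0.84 |
| Control | 109 | 7.2 (5.4) | 7.1 (5.4) | 0.86 |

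The quantity is P(screening ≥ 5 | visit < 5) = 1 − P(both < 5)/P(visit < 5).

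- *Bivariate normal, cut at 4.5.* IMCP 1 − 0.192/0.268 = 0.286; PSA 1 − 0.243/0.339 = 0.284; control 1 − 0.236/0.315 = 0.250. Called: 25.7 + 31.0 + 27.2 = 83.9 of 308. The fit is imperfect: the model puts 0.268/0.339/0.315 below 5 at the visit, against an observed 0.306/0.381/0.380 with PHQ-9 < 5.
- *Negative-binomial margins with a Gaussian copula.* 0.260, 0.259, 0.218. Called: about 75 of 308. This model puts 0.306/0.412/0.377 below 5 at the visit.

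So about 22% to 29% by arm. Neither model represents the score-dependent sampling at screening, so a range of 10% to 50% (31 to 154 called) is carried forward.

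**4. Power for 0.4 SD at 12 weeks.** Two-sample t-test, two-sided 5%, arm sizes = share × (90; 109; 109). The adjusted column divides d by √(1 − 0.7²) = 0.714, for an assumed baseline correlation of 0.7.

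| Share called | Unadjusted, IMCP; PSA vs control | Adjusted, IMCP; PSA vs control |
|---|---|---|
| 100% | 0.80; 0.84 | 0.98; 0.98 |
| 50% | 0.50; 0.54 | 0.79; 0.83 |
| 25% | 0.28; 0.31 | 0.49; 0.53 |
| 10% | 0.13; 0.14 | 0.22; 0.24 |

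Pooling the active arms against control gives 0.92 unadjusted if all are called and 0.38 at a 25% share.

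**5. Detectable difference at 80% power.** Using the SF-12 physical SD of 13.2 from the whole control arm in Table 2 (assumed to apply to Sub-study 2):

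- All called, unadjusted: 0.40 and 0.38 SD, or 5.3 and 5.0 points.
- 25% called, unadjusted: 0.81 and 0.77 SD, or 10.8 and 10.2 points.
- 25% called, adjusted: multiply by 0.714, giving 7.7 and 7.3 points.

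Clustering by physician and non-response at 12 weeks are ignored; non-response would lower power further.

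**The case against.** The best reply is that this is a narrow mismatch of text on an outcome that is not the key one. Several parts of that reply stand, and they rule out stronger readings.

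- **That the article gives several incompatible accounts of follow-up.** A reader might set the abstract's "Patient surveys were also collected immediately post-visit and 12 weeks later" and the Table 1 abbreviation "not applicable (participants in this sub-study are not followed up" against the call rule. The abstract sentence does not say that everyone was surveyed. The abbreviation is used in no cell of the table as shown and names no sub-study. The consent description also speaks only of possible contact at 12 weeks. The real conflict is between the call rule on one side and aim 1(b) and Table 1 on the other.
- **That the power statement is wrong.** It is conditional on 102 per arm and names no outcome. It holds for Sub-study 2 post-visit means such as stigma. It only fails to transfer to 12 weeks.
- **That being called depends on arm.** A reader might infer a post-visit trigger, because the post-visit questionnaire is one "which contained many of the same items as on the pre-visit questionnaire". But Table 1 has no PHQ-8 row for Sub-study 2, and Table 2 lists the index-visit PHQ-8 among baseline characteristics. The natural reading is the previsit score. On that reading both triggers precede exposure to the intervention, and the arm contrast within the called subset is not biased by the rule.
- **That power is as low as the unadjusted figures.** SF-12 was measured at enrollment and repeated-measures models are planned, so adjustment could recover much of the loss. At a 50% share and correlation 0.7, power is back near 80%. At the illustrative 25% it is not.

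Also, Sub-study 2 is defined by a single baseline score. The article does not say that it is meant only for persistently symptom-free patients. And 12-week stigma is only a Table 1 mark, since aim 2's hypothesis concerns stigma after the index visit.

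None of this removes the mismatch. An analysis plan could restrict the analysis set, but it could not supply interviews that were never held.

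**Conclusion.** The point holds in limited form. As written, the call rule supplies 12-week SF-12 physical health and stigma for only a selected part of Sub-study 2, while aim 1(b) and Table 1 set them for all of it. The logical step is certain if the index-visit score is the previsit score. The size is not: it rests on an assumed share called, with 22% to 29% as an illustration and 10% to 50% as the range. At 25%, power for 0.4 SD is about 0.3 unadjusted and about 0.5 with an assumed correlation of 0.7.

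The consequence is for interpretation. A 12-week contrast would describe patients who screened at 5 or more and were below 5 at the visit, with too little precision to show absence of harm. The document does not support the reading that the trial's hazard assessment as a whole fails: the antidepressant noninferiority test and the post-visit outcomes use index-visit data, as does the key outcome in Sub-study 1. It is worth correcting, but it does not threaten the main results.

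**What to change.** The calls are described in the past tense, so the text should be made to match what was done.

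1. If the call rule is accurate, restrict the 12-week Sub-study 2 outcomes in aim 1(b) and Table 1 to patients with previsit PHQ-9 < 5 and screening PHQ-8 ≥ 5. Give the number called in each arm and label these outcomes exploratory.
2. In the power section, state that the 0.4 SD figure at 102 per arm does not apply to them.
3. Do not use them as evidence of no 12-week harm in the non-depressed sub-study as a whole. The planned 95% confidence intervals can be reported for the subset.
4. State in the call rule that the index-visit score means the previsit score.
5. If all of Sub-study 2 was in fact called, correct the call rule instead; items 1 to 3 then fall away.

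The cost is edits in four places (aim 1(b), Table 1, the call rule, the power section) and one count per arm. The price is giving up a 12-week physical-function safety claim for the whole sub-study, which the calls as described could not support.
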